#### Safety analysis

All patients who receive any study treatment will be included in the safety analysis. AEs will be recorded at each visit and graded according to the NCI-CTCAE version 5.0. The incidence of all AEs, SAEs, and treatment-related AEs will be summarized in frequency tables by system organ class and preferred term, with the number and percentage of patients affected in each category. Key adverse event rates, such as the incidence of Grade 3 or higher toxicities, will be reported with corresponding 95% confidence intervals. Events that lead to dose reductions or permanent treatment discontinuation will be tabulated or listed separately. Particular attention will be given to events of special interest in this combination regimen, including immune-related AEs and any toxicities attributable to HBOT. In the absence of a control arm, the safety data will be interpreted descriptively and may be compared qualitatively to historical safety data from similar treatment regimens.

Clinical laboratory test results and vital signs will be monitored for changes of clinical significance over time. Continuous laboratory parameters will be analyzed for changes from baseline using paired statistical tests: if a parameter is approximately normally distributed, a paired t-test will be used; if not, the Wilcoxon signed-rank test will be used as a non-parametric alternative. Summary statistics (mean ± SD or median with IQR) for laboratory values may be presented at baseline and at post-baseline time points, along with the change from baseline. Categorical shifts in laboratory values (such as the proportion of patients whose results shift from normal to abnormal ranges) will be summarized as counts and percentages in contingency tables.

##### Exploratory Biomarker Analysis

Biomarker samples will be collected at prespecified time points from tumor tissue, peripheral blood, and fecal material (see **Supplementary File 1** for detailed collection and analysis procedures). Key exploratory biomarkers include tumor tissue parameters (intratumoral CD8^+^T-cell density and expression of hypoxia-related markers HIF-1α and CAIX), peripheral blood immune cell subsets (CD4^+^ and CD8^+^ T-cell percentages and the CD4:CD8 ratio), and baseline gut microbiome diversity indices (the Shannon diversity index from fecal samples). All biomarker analyses will be descriptive and hypothesis-generating. Analyses will be performed on the subset of patients who have evaluable data for both the biomarker and clinical outcome of interest; for each biomarker endpoint, the number of patients with available data (n/N) will be reported. We will explore changes in biomarker levels over time and their associations with clinical outcomes, but these exploratory findings will be interpreted with caution. No formal hypothesis testing is planned for biomarker endpoints in the main analysis.

#### Subgroup analyses

No inferential subgroup comparisons or covariate-adjusted analyses are planned due to the limited sample size. However, to aid clinical interpretation, key efficacy outcomes will be presented descriptively across several predefined patient subgroups (display-only analyses for exploratory purposes). Subgroups of interest include: (i) tumor location (gastric vs gastroesophageal junction), (ii) presence of baseline liver metastases (yes vs no), (iii) PD-L1 combined positive score (CPS ≥1 vs <1, with an additional exploratory cut-off of CPS ≥5 vs <5 if sample size permits), and (iv) tumor MMR status (pMMR vs dMMR). Within each subgroup, ORR will be reported as n/N (%) with two-sided 95% exact confidence intervals (Clopper–Pearson method). The absolute difference in response rates between subgroup categories and the corresponding odds ratio will also be provided as point estimates without calculation of p-values or formal statistical tests. PFS in each subgroup will be illustrated using Kaplan-Meier curves and summarized by the median PFS (with 95% CI). Patients missing the relevant subgroup or biomarker information will be excluded from that subgroup analysis, and no data imputation will be performed for missing subgroup classification variables. All subgroup analyses are considered exploratory and descriptive; no significance tests or interaction tests will be conducted, and these subgroup results will not affect the pre-specified primary and secondary endpoint analyses.

#### Sensitivity analyses and missing data

##### Sensitivity analyses

The robustness of the primary endpoint analysis will be examined through predefined sensitivity analyses. In addition to the main ORR analysis conducted on the ITT population, the ORR will also be calculated for the PP population to evaluate the impact of any protocol deviations on the primary outcome. Furthermore, as an exploratory sensitivity analysis concerning PD-L1 status, the effect of using an alternative PD-L1 expression cutoff will be assessed: specifically, outcomes will be examined using a CPS threshold of 5 (CPS ≥5 vs. <5), as was prespecified before the trial.

##### Missing data

For the primary endpoint ORR in the ITT population, patients who have no post-baseline tumor assessments will be counted as non-responders. For time-to-event endpoints such as PFS, DFS, or OS, patients who have not experienced the event by the cutoff date will be censored at the time of their last adequate disease assessment. If scheduled visits or assessments are missed, all data collected up to the point of patient withdrawal or loss to follow-up will be included in the analysis, and no forward imputation of missing future observations will be performed. Missing data in patient-reported outcome measures, such as QoL questionnaires, will not be imputed; analyses will be based on available data only.

To address the potential impact of missing data, we may conduct additional exploratory analyses using methods that accommodate data missing at random. For example, a linear mixed-effects model for repeated measures could be employed to explore longitudinal trends in QoL scores despite some missing follow-up data. If more than 10% of patients have missing data for the primary endpoint, we will perform additional sensitivity analyses to ensure the robustness of our conclusions. These may include using multiple imputation techniques to estimate missing outcomes and conducting best-case and worst-case scenario analyses to gauge the potential range of impact due to the missing data.

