**Figure 1 f1:**
[figure not shown]
SPIRIT figure. SPIRIT showing the schedule of enrollment, interventions, and assessments in the Phase Ib/II single-arm trial evaluating XELOX, sintilimab, and HBOT in patients with HER2-negative advanced or metastatic GC/GEJC. The timeline encompasses initial screening procedures and baseline data collection, followed by six 21-day cycles of therapy in which oxaliplatin and sintilimab are administered intravenously on Day 1 of each cycle, capecitabine is given orally on Days 1–14 of each cycle, and HBOT at 2.0 atmospheres absolute for 60 minutes is delivered on Day 1 after the drug infusions. After completing six cycles, patients transition to a maintenance phase with capecitabine and sintilimab only. Radiologic tumor evaluations are performed every two cycles until disease progression, and biomarker specimens are collected at predefined time points, including an optional tumor biopsy at progression. Throughout the study, each cycle includes pre-treatment laboratory tests, tumor marker measurements, and ECOG performance status assessments, and all adverse events are closely monitored.

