Secondary efficacy endpoints will be analyzed and reported descriptively. PFS is defined as the time from treatment initiation until radiologic disease progression or death. It will be estimated using the Kaplan-Meier method; the median PFS and its two-sided 95% confidence interval will be reported. Patients who are alive without progression at the time of analysis will be censored at the date of their last disease assessment. DCR is the percentage of patients achieving CR or PR or sustained stable disease for at least 6 weeks. DCR will be reported with a two-sided 95% exact confidence interval calculated by the Clopper-Pearson method. For the subset of patients who undergo curative-intent surgery (R0 resection) after successful therapy, a 2-year DFS rate will be calculated. This rate will be defined as the proportion of those post-surgery patients who are alive and recurrence-free 24 months after surgery. Because this subset is expected to be small, the 2-year DFS will be presented as a descriptive metric without formal statistical comparison. OS is defined as the time from treatment initiation until death from any cause. The 24-month OS rate will be estimated using Kaplan-Meier methods, and if sufficient follow-up is available, the median OS and its 95% confidence interval will also be reported. If the median OS is not reached by the analysis time, the survival rate at the last follow-up time point will be provided instead. Patients who are alive at the time of analysis (or last known follow-up) will be censored on that date for OS and DFS analyses. Patient-reported quality of life outcomes will be summarized at baseline and at specified time points during treatment. Changes from baseline in QoL scores may be explored with paired statistical tests, depending on data distribution, as an exploratory analysis.

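### Two sections give different censoring dates for OS and DFS, and the Missing data rule, applied to OS, biases two-year OS downward

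*Protocol article*

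**What the plan says.** Two places in the Statistical analysis part of the protocol article set censoring dates.

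- **Efficacy endpoints.** For PFS: "Patients who are alive without progression at the time of analysis will be censored at the date of their last disease assessment". For the other two: "Patients who are alive at the time of analysis (or last known follow-up) will be censored on that date for OS and DFS analyses". The same section fixes the OS event ("OS is defined as the time from treatment initiation until death from any cause") and the estimator ("The 24-month OS rate will be estimated using Kaplan-Meier methods"). It reports two-year DFS as a simple proportion among patients with R0 resection.
- **Missing data.** "For time-to-event endpoints such as PFS, DFS, or OS", it says, "patients who have not experienced the event by the cutoff date will be censored at the time of their last adequate disease assessment".

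The Figure 1 legend adds the fact that decides which date suits OS: "Radiologic tumor evaluations are performed every two cycles until disease progression".

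**The concern.** OS and DFS are named in both places with different dates, and nothing says which sentence governs. Only PFS is consistent. Two analysts who each follow the text could report different two-year OS figures from the same data.

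The two dates are not equally sound for OS. Kaplan–Meier needs censoring to be unrelated to prognosis. If survivors are cut back to their last scan, and scanning ends at progression, post-progression time is removed from survivors only. The patients who died after progression keep theirs and count as events. That makes the OS estimate too low.

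For DFS the problem lies in the other sentence and is softer. It conditions only on being alive, so time after the last recurrence assessment may be credited as disease-free.

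**Working it through.** **1. The rules side by side**

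| Endpoint | Efficacy endpoints | Missing data | Agree? |
|---|---|---|---|
| PFS | last disease assessment | last adequate disease assessment | yes |
| OS | analysis date or last known follow-up, if alive | last adequate disease assessment | no |
| DFS | analysis date or last known follow-up, if alive | last adequate disease assessment | no |

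**2. Mechanism for OS.** Take two patients who progress at the same scan. One dies later; the other is still alive at the cutoff, after that death. If the survivor is censored when last known alive, two patients are at risk at the death and the survival estimate is multiplied by 1 − 1/2. If the survivor is censored at the progression scan, only one is at risk and it is multiplied by 1 − 1/1 = 0. A survivor who has not progressed loses little, at most about one scan interval. The bias therefore comes from post-progression survivors.

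**3. Size for OS.** The article states no figure to reproduce and gives no survival inputs, so this is an illustration.

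- From the article: scans every two 21-day cycles, i.e. 42 days, until progression; accrual from 31 December 2024 to about 31 December 2026, i.e. 24 months, taken as uniform.
- Assumed: exponential PFS (median 7 or 9 months); exponential post-progression survival (median 8 or 10 months); a share q = 10% or 20% of PFS events being deaths; data cut 12, 24 or 36 months after last enrolment.

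True 24-month OS, with a = ln 2/(median PFS) and b = ln 2/(median post-progression survival):

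S(24) = e^(−24a) + (1 − q) · a/(a − b) · [e^(−24b) − e^(−24a)]

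For medians 7 and 8 with q = 10%: e^(−24a) = 2^(−24/7) = 0.0929; e^(−24b) = 2^(−3) = 0.1250; a/(a − b) = 8. So S(24) = 0.0929 + 0.9 × 8 × 0.0321 = 0.324.

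Kaplan–Meier 24-month OS under the Missing data rule, by large simulation (200,000 to 400,000 patients per scenario; repeat runs differ by about 0.1 point):

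| Median PFS / post-progression, q | True | Cut +12 mo | Cut +24 mo | Cut +36 mo |
|---|---|---|---|---|
| 7 / 8, 10% | 32.4% | 21.3% | 27.5% | 30.8% |
| 7 / 8, 20% | 29.8% | 19.7% | 25.3% | 28.3% |
| 9 / 10, 10% | 44.5% | 32.8% | 38.8% | 42.3% |
| 9 / 10, 20% | 41.3% | 30.6% | 36.1% | 39.3% |

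The shortfall is about 10–12 points at +12 months, 4.5–6 at +24 and 1.5–2.5 at +36. At +12 months median OS is 1.6–3.2 months too short. Censoring at the date last known alive returns the true rate in every row. These rows pair 7 with 8 and 9 with 10; crossing the pairs (7 with 10, 9 with 8) widens the ranges to about 9–14, 4–7 and 1–3 points.

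A second set of assumptions (median PFS/OS of 6/12, 7/15 and 9/18 months, no deaths before progression) gives 1 to 11 points over minimum follow-up of 6 to 24 months. For 7/15 the true 25.3% becomes 15.0%, 18.3% and 22.8% at 6, 12 and 24 months.

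**4. DFS.** Suppose DFS were estimated by Kaplan–Meier, median DFS were 12–24 months, and 10–30% of patients stopped scans while known alive (all assumptions). Censoring at the alive date would then put 24-month DFS about 2–9 points too high; censoring at the last assessment is unbiased in the same simulation. The article reports a proportion, so these figures show direction only.

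**The case against.** The strongest case on the other side is that the sound OS rule is already in the endpoint-specific text, and the Missing data sentence is a generic one into which OS slipped. A careful analyst might simply follow the specific text. But OS is named in the generic sentence and no precedence is given, so the conflict stands.

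On size, the 10–12 point figure needs a cut 12 months after last enrolment, when some patients could not yet have 24 months of follow-up. For a two-year endpoint a later cut is at least as natural. With 48 patients and a rate of 32.4%, the binomial standard error is √(0.324 × 0.676/48) = 0.068, about 7 points, so at +24 months the bias in the tabulated scenarios is below one standard error. That is fair, and it is why the whole range is given. The bias is nevertheless systematic and always in the same direction.

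On DFS, the objection largely stands. Last known follow-up could mean recurrence follow-up; the reported figure is a proportion in a subset expected to be small; and the Figure 1 scan schedule does not describe imaging after resection. A reader might infer that the DFS rule is plainly wrong. The text supports only that it is ambiguous.

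A reader might also infer that a biased OS would distort a comparison with history. The article plans a qualitative historical comparison for ORR and allows one for safety, but states none for OS.

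**Conclusion.** The contradiction is real for OS and DFS, and the Missing data rule is unsuitable for OS because it makes censoring depend on outcome. The direction, two-year OS too low, follows from scans ending at progression. The size depends on survival and data-cut assumptions that the article does not supply: in the tabulated scenarios about 10–12, 4.5–6 and 1.5–2.5 points at cuts 12, 24 and 36 months after last enrolment. For DFS the finding is an ambiguity that may credit unassessed time as disease-free, with limited effect on a descriptive proportion in a small subset.

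Severity is moderate. It would be tempting to say that the conflict undermines the trial's main result; it does not. ORR has its own consistent rule for missing assessments, and OS and DFS carry no hypothesis test.

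**What to change.** State one rule per endpoint, worded identically in both sections:

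- **OS:** censor at the date last known alive. Delete OS from the Missing data sentence.
- **PFS and DFS:** censor at the last adequate disease assessment without progression or recurrence. Delete DFS from the Efficacy endpoints sentence on patients who are alive.

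When DFS is edited, also say how a resected patient without 24 months of recurrence follow-up counts in the proportion.

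The cost is two sentences of wording. No new data are needed, provided survival status is collected after progression, which two-year OS as defined already requires. Recruitment is expected to run to about the end of 2026, so the change can be made before the analysis.

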#### Phase Ib analysis

In the Phase Ib safety run-in portion, no formal statistical hypothesis testing will be performed due to the small sample size. Selection of the recommended Phase II dose (RP2D) HBOT regimen will be guided primarily by safety and tolerability outcomes (the occurrence of any DLTs during the first treatment cycle, the incidence of ≥Grade 3 HBOT-related adverse events, and the frequency of treatment interruptions or dose reductions attributable to toxicity). Feasibility metrics, such as patient adherence to the HBOT schedule (compliance rate and completion of planned sessions), and preliminary efficacy signals (ORR and DCR, assessed descriptively) will also be taken into account in determining the RP2D. If multiple HBOT regimens exhibit similar safety profiles, the regimen with better feasibility and a more favorable preliminary efficacy trend will be selected for progression to the Phase II trial.

### Recruitment strategies

Participants will be recruited from the outpatient and inpatient services of the West China Hospital, Sichuan University. Eligible patients will be identified through referral by treating oncologists, review of clinic schedules, and pre-screening of electronic medical records.

## Discussion

The treatment landscape for advanced GC/GEJC has entered the era of immunotherapy. Compared with chemotherapy alone, combining ICIs with chemotherapy has been shown to prolong OS and PFS as a first-line treatment for advanced or metastatic GC/GEJC. This combination is recommended as a standard treatment in most guidelines (3–5, 25). However, response rates to ICI and chemotherapy combinations remain modest, and many patients who initially respond quickly develop resistance, resulting in overall efficacy that falls short of clinical expectations. Therefore, there is an urgent need for new combination treatment strategies. Although various ICI-sensitizing combination therapies are in different stages of clinical research, existing data suggest that these strategies often lead to higher rates of adverse reactions (26, 27). In contrast, HBOT can improve the hypoxic tumor microenvironment by enhancing drug delivery to the tumor, promoting the infiltration of CTLs, and reversing the immunosuppressive environment, thereby increasing antitumor responses (11–13). Additionally, compared with other combination therapies, HBOT has fewer contraindications, lower rates of adverse reactions, and a lower economic burden, making it a highly promising treatment strategy.

We reviewed clinical studies on the use of HBOT in cancer treatment. Although evidence suggests that HBOT can enhance the efficacy of radiotherapy and chemotherapy, studies are limited and often involve small sample sizes, with HBOT primarily used as an adjunct to these therapies. For example, Hongmei Xing reported that, compared with control patients, postoperative glioma patients receiving HBOT combined with chemotherapy presented significantly improved motor function (FMA) and activities of daily living (ADL) scores. In radiotherapy, HBOT has been shown to significantly reduce radiation-induced proctitis and cystitis and prevent radiation-induced osteonecrosis (28, 29). These studies indicate that HBOT combination therapies may not increase adverse reactions and may even improve patients’ quality of life. In our trial, including quality-of-life as a secondary endpoint allows us to directly evaluate this aspect. If improved QoL is observed alongside tumor response, it will underscore the patient-centered benefits of adding HBOT. This information can guide clinicians in weighing the regimen’s value beyond traditional efficacy metrics.

In our previous studies of advanced GC/GEJC, we observed that a subset of patients became eligible for surgery after systemic therapy. To further evaluate long−term benefit in this patient cohort, we will prospectively follow patients who undergo surgery and include two−year DFS as a secondary endpoint restricted to those converted to resectable disease and achieving an R0 resection. This endpoint is intended to assess the durability of disease control and the potential curative benefit of conversion therapy.

Currently, there is no consensus on the optimal pressure and oxygen duration for the use of HBOT in tumor treatment. Our review of multiple clinical and preclinical studies revealed that most used pressures between 2.0–2.5 ATA and oxygen inhalation times of 30–90 minutes (29–33). For gastrointestinal tumors, Qi Sun et al. administered HBOT at 2.0 ATA for 60 minutes, and the results demonstrated good safety and a lower incidence of adverse reactions than in controls. Owing to the significant variability in HBOT treatment protocols, our study employs a 3 + 3 dose-escalation design and a single-arm exploratory approach to assess the safety, tolerability, and preliminary efficacy of HBOT combined with chemotherapy and ICIs in the early stages. This phased assessment will help optimize treatment strategies and provide a solid data foundation for future randomized controlled trials.

As a key intervention in this study, HBOT may offer substantial antitumor benefits but can also cause potential adverse reactions, such as pneumothorax, ear barotrauma, chest tightness, headaches, and blurred vision (34). Therefore, strict monitoring of patients during treatment is essential, particularly for respiratory status and ear responses. Early identification of adverse reactions, rational treatment design, and timely interventions can effectively minimize HBOT risks and ensure patient safety. Additionally, the potential for organ-specific adverse events in GC/GEJC patients receiving HBOT is unknown, necessitating close monitoring throughout treatment.

However, this study has several limitations. It is designed as a single-arm, single-center clinical trial without a control group, which limits the ability to directly attribute observed clinical outcomes to the addition of HBOT. The relatively small sample size may restrict the statistical power and the generalizability of the findings to broader populations. Furthermore, the open-label nature of the trial and potential biases related to patient selection and center-specific clinical practices cannot be completely excluded. These limitations should be considered when interpreting the results and planning future confirmatory studies.

In summary, we are conducting a prospective, single-center, single-arm phase Ib/II clinical trial to evaluate the efficacy and safety of HBOT combined with chemotherapy and immunotherapy in HER2-negative advanced or metastatic GC/GEJC. To our knowledge, no clinical studies have reported the use of HBOT combined with ICIs for tumor treatment, suggesting a novel therapeutic strategy for patients with advanced GC/GEJC.

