**Methods:**

This prospective, single-center, single-arm phase Ib/II trial evaluated the efficacy and safety of the XELOX regimen combined with sintilimab and HBOT in HER2-negative advanced or metastatic GC/GEJC patients. Phase Ib employs a 3 + 3 dose-escalation design with nine patients to assess safety and determine the optimal HBOT protocol. Phase II will enrol 48 patients, accounting for a 5% dropout rate, with a focus on the ORR as the primary endpoint. The secondary endpoints include progression-free survival (PFS), the disease control rate (DCR), 2-year disease free survival (DFS), two-year overall survival (OS), quality of life (QoL), and safety. All participants received XELOX, sintilimab and HBOT. Efficacy is assessed every two cycles, with maintenance therapy continuing until disease progression or other termination criteria are met.

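### The Discussion reads improved QoL alongside tumour response as a benefit of adding HBOT, which a single arm with only within-arm QoL change cannot show and which conflicts with the article's own limitation.

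*Protocol article*

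**What the plan says.** QoL is a named secondary endpoint of Phase II (Abstract; Endpoints). The Discussion cites earlier HBOT studies as a sign that HBOT combinations may improve QoL. It then adds: "In our trial, including quality-of-life as a secondary endpoint allows us to directly evaluate this aspect". The next sentence gives the reading of a favourable result: "If improved QoL is observed alongside tumor response, it will underscore the patient-centered benefits of adding HBOT". The article goes on to say that this information can help clinicians judge what the regimen is worth.

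The design and analysis text bearing on that reading is:

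- **Treatment (Abstract, Methods):** "All participants received XELOX, sintilimab and HBOT". There is no arm without HBOT.
- **QoL analysis (Efficacy endpoints):** scores are summarized at baseline and during treatment. "Changes from baseline in QoL scores may be explored with paired statistical tests, depending on data distribution, as an exploratory analysis".
- **Missing QoL data (Missing data):** these "will not be imputed; analyses will be based on available data only", with a mixed model mentioned only as a possible extra.
- **Limitations (Discussion):** the trial is described as being "without a control group, which limits the ability to directly attribute observed clinical outcomes to the addition of HBOT".

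For ORR (Efficacy endpoints) and for safety (Safety analysis), the article confines any outside comparison to a qualitative one with historical data. It says nothing equivalent for QoL.

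**The concern.** The credit in the Discussion goes to the addition of HBOT, not to the regimen. The evidence named for it is two observations from patients who all received everything: a QoL change and the presence of responses. XELOX plus sintilimab, supportive care or the passage of time could produce both. An HBOT effect, if there is one, would be part of what is observed, but the data offer no way to separate it out.

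At stake is what the trial may conclude on a named secondary endpoint. Read as written, a favourable QoL course would be reported to clinicians as an HBOT benefit, although the same Discussion warns against that kind of attribution.

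**Working it through.** **1. The passages side by side.** One paragraph of the Discussion says that "including quality-of-life as a secondary endpoint allows us to directly evaluate this aspect" and names the benefit of adding HBOT as the conclusion. The limitations paragraph says the absence of a control group is something "which limits the ability to directly attribute observed clinical outcomes to the addition of HBOT". QoL is an observed clinical outcome, so the caveat covers it. The caveat is general, however, and does not withdraw or qualify the specific sentence.

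**2. The plan's own figures.** The documents give no QoL effect size, SD or threshold, so there is no QoL figure to reproduce. The only sizing is for ORR (Methods): 58% without HBOT, 73% with it, two-sided alpha 0.20, power 80%. The normal approximation gives

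n = [(1.2816·√(0.58·0.42) + 0.8416·√(0.73·0.27)) / 0.15]² = 44.99, so 45.

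Allowing 5% attrition, 45/0.95 = 47.4, so 48. The stated 45 and 48 reproduce. I use n = 48 and the no-HBOT ORR of 58% below.

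**3. Does tumour response add discrimination?** If HBOT does nothing and ORR is 58%, the chance of no response among 48 patients is 0.42^48, below 10^-18. The presence of responses is therefore practically certain without any HBOT effect. If the sentence is taken to mean an ORR of at least 58% (28 of 48), the probability is 0.543.

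**4. How often would the sentence apply if HBOT had no effect?** Let d be the mean QoL change on the XELOX plus sintilimab background, in SD units of the change score. The documents do not give d, so it is an assumed range. The true HBOT contribution is set to zero.

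- Any positive mean change: P = Φ(d·√48), with √48 = 6.928. For example, at d = +0.1, Φ(0.693) = 0.756.
- Also requiring ORR of at least 58%: multiply by 0.543, treating QoL and response as independent (a simplification).
- Requiring instead a paired test significant at two-sided 5% in the improving direction: P ≈ 1 − Φ(1.960 − d·√48).

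| d (SD) | Mean change > 0, any response | Mean change > 0, ORR ≥ 58% | Significant paired test, any response |
|---|---|---|---|
| -0.3 | 2% | 1% | 0% |
| -0.2 | 8% | 5% | 0% |
| -0.1 | 24% | 13% | 0.4% |
| 0 | 50% | 27% | 2.5% |
| +0.1 | 76% | 41% | 10% |
| +0.2 | 92% | 50% | 28% |
| +0.3 | 98% | 53% | 55% |

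The last column uses the normal approximation. The noncentral t distribution gives 10%, 27% and 53% at +0.1, +0.2 and +0.3 SD.

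**5. Fewer patients with QoL data.** With n = 30, the first column becomes 5%, 14%, 29%, 50%, 71%, 86% and 95%. The pattern is the same, drawn slightly toward 50%. Because the main QoL analysis uses available data, an observed mean could also shift upward if patients doing badly stop returning questionnaires. The documents give no figure for this and I have not put one in.

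**The case against.** The strongest reply is that this is a remark in a Discussion, not part of the analysis. It carries no criterion, test or action. The analysis section makes efficacy results descriptive and QoL tests optional and exploratory, and the limitations paragraph already discloses the attribution problem. The phrase about direct evaluation can be read as concerning QoL under HBOT combinations, which a single arm can measure. Most of this stands, and it is why the point is small. It does not rescue the sentence that follows, which names the addition of HBOT as the thing shown.

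Three stronger readings are tempting and are not supported:

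- *That the article sets a formal decision rule for QoL.* It does not. The sentence is an interpretive statement, and the probabilities above attach assumed criteria to it.
- *That the observations are unrelated to any HBOT effect.* They would include one if it existed. The correct statement is that they do not require it and cannot isolate it.
- *That the sentence would be wrong in half or more of trials, or has a high false-positive rate.* That needs a flat or rising background QoL and a lenient criterion. QoL could fall on cytotoxic chemotherapy, and the rate is then well below half.

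Nor does the limitations paragraph say that attribution is impossible. It says attribution is limited. The conflict is between an unqualified claim and that caveat.

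**Conclusion.** The point holds in a limited form. The Discussion credits a favourable QoL result to adding HBOT, the design can describe QoL only under the full combination, and the article's own limitation says as much in general terms. This conclusion follows from the text and does not depend on any assumed QoL figure.

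The size of the risk is not fixed by the documents. With n = 48, zero HBOT effect and any positive mean counted, it runs from about 2% to 98% as the background change goes from -0.3 to +0.3 SD. A required significant paired test lowers it to about 2.5% at zero, and it rises to about 53% at +0.3 SD. No single rate should be quoted without those conditions.

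Severity is minor: no endpoint, sample size or planned analysis changes, only what may be concluded from a secondary endpoint.

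**What to change.** Reword the QoL sentences in the Discussion along these lines:

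> *Change in QoL from baseline describes the complete XELOX, sintilimab and HBOT regimen. Improvement, with or without tumour response, will not by itself be interpreted as a benefit of adding HBOT. Any contrast with data from patients not given HBOT will be qualitative. The effect of HBOT itself on QoL is left to future randomized trials.*

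The phrase about direct evaluation can stay if its object is made QoL under the combination. The qualitative limit matches what Efficacy endpoints and Safety analysis already provide for ORR and safety, and the Discussion already looks ahead to randomized trials.

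The change needs no new data, patients or analysis. Its cost is a favourable claim about HBOT and QoL that the trial could otherwise have made.
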